### Cardiac arrest location and public access defibrillation (PAD) programs

Following the publication of the Public Access Defibrillation (PAD) trial in 2004 [9], PAD programs received the highest endorsement from the American Heart Association. This study randomized community units to one of two emergency response systems consisting of either lay volunteers trained in CPR alone, or in CPR and the use of Automatic External Defibrillators (AED). Survival to hospital discharge from a cardiac arrest occurring in a public location increased as a result of the AED program [Relative Risk 2.0 (95% CI 1.07 to 3.77); P = 0.03] [9].

Unfortunately, since 85% of all cardiac arrests occur in a residential location [2], even the highest achievable survival rate in the remaining 15% of cardiac arrests occurring in a public location would have a limited impact on overall cardiac arrest survival. Stakeholders should consider the issues surrounding the implementation of a residential-access defibrillation program, and/or an alternative intervention most susceptible to improve bystander CPR rates in residential locations.

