**Figure 1 F1:**
[figure not shown]
Study design and proposed statistical analyses.

The study will take place in 19 large and small cities located in Ontario, Canada affiliated with 11 base hospital programs. The combined population in those 19 communities is 2,903,887 and ranges between 15,605 and 774,072 (2001 Statistics Canada census). Approximately 1,703 patients suffer cardiac arrest each year and receive treatment in these communities. All communities have sophisticated EMS services with first responding fire fighters and second-tier primary care (BLS-D) and advanced care (ALS) paramedics. All centres have been collecting high-quality data on system and cardiac arrest victim characteristics since 1994, and all have initiated dispatch-assisted CPR instructions between 2004 and 2005.

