#### Bystander CPR and Survival Rates

Descriptive statistics with 95% CIs will be calculated for bystander CPR and survival rates. In addition, two statistical modelling approaches will be considered: 1) A univariate and a stepwise logistic regression analysis to control for potential confounding effects of variables possibly associated with bystander CPR and survival rates. These variables include age, gender, initial cardiac rhythm, and EMS response time intervals. Bystander CPR rates and cardiac arrest survival rates in the "before" phase (prior to 2004) will be compared to the "after" phase (after the run-in period finishing in 2006) controlling for these confounding variables. 2) A time series analysis to analyse trends (quarterly) over the whole study period (including the run-in phase), and identify a possible point of inflection due to the implementation of dispatch-assisted CPR instructions. This will determine if bystander CPR and survival rate inflections are significant, controlling for trends over time. This analysis will be performed for each community and then the results may be combined in a meta-analysis after assessing homogeneity of the results across the communities.

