### Sample size

The main objective of this study is to measure the effect of dispatch-assisted CPR instructions on survival to hospital discharge for out-of-hospital cardiac arrest victims. The required sample size has been estimated based on a dichotomous response variable from two independent samples (before and after the introduction of dispatch-assisted CPR instructions). The required sample size is based on an expected survival rate of 5% in the before group (based on previous studies conducted in the study communities [8]), an expected survival rate of 7% in the after group (based on mathematical modelling and scientific reports), an average survival rate of 6% for all study participants and a 2% minimal clinically important difference in survival rate. Using these figures and setting power at 90%, 2,962 cardiac arrest victims will be required for each group.

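### The only survival analysis stated to control for time trends is run community by community on about one survivor per quarter, with pooling optional and the change point not set in advance

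*Protocol article*

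**What the plan says.** The Data analysis subsection on bystander CPR and survival offers two modelling approaches.

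- **Logistic regression (univariate and stepwise).** It compares the period before 2004 with the period after the run-in ends in 2006. The variables named are age, gender, initial rhythm and EMS response intervals. Neither calendar time nor community is named.
- **Quarterly time series over the whole period, run-in included.** Its task is to "identify a possible point of inflection due to the implementation of dispatch-assisted CPR instructions", and it is the only analysis described as controlling for trends. On the unit of analysis and pooling: "This analysis will be performed for each community and then the results may be combined in a meta-analysis after assessing homogeneity".

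Study design and setting says of the 19 communities that "all have initiated dispatch-assisted CPR instructions between 2004 and 2005". It also gives about 1,703 treated arrests a year and data collection since 1994. No start date is given for the before series.

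The Sample size section makes survival to discharge the main objective. It sizes a comparison of two independent proportions: "an expected survival rate of 5% in the before group", "an expected survival rate of 7% in the after group", and "setting power at 90%, 2,962 cardiac arrest victims will be required for each group".

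**The concern.** The before and after phases are separated by 2004–2006, and other things may have changed in that gap. A simple comparison credits all of them to the programme unless a covariate absorbs them. Separating the programme from secular change therefore falls to the time series, and for survival its stated form is weak in three ways.

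1. The unit is the single community, where quarterly survivor counts are mostly very small.
2. Combining communities is permitted rather than promised, and it follows a homogeneity assessment that such imprecise estimates cannot inform.
3. The change point is left to be identified from the data, although the start of the instructions is a known event in each community.

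At stake is the main objective. If the community results are inconclusive and are not combined, the survival conclusion would rest on the comparison that has no stated protection against trend.

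**Working it through.** **The plan's own figure.** Inputs from Sample size: 5%, 7%, mean 6%, difference 2 points, power 90%. Alpha is not stated, so two-sided 0.05 is assumed.

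n = [1.960·√(2·0.06·0.94) + 1.282·√(0.05·0.95 + 0.07·0.93)]² / 0.02² = 2,961.02, rounded up to 2,962 per group. The figure reproduces. The formula has no trend and no community term, so the 90% belongs to that simple contrast.

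**Events per community-quarter.** Inputs from Study design and setting: 1,703 arrests a year, 19 communities, total population 2,903,887, smallest 15,605, largest 774,072. Scaling arrests to population is an assumption.

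- Average: 1,703/(19·4) = 22.4 arrests; ×0.05 = 1.12 survivors. Under a Poisson count, a quarter has no survivor with probability e^(−1.12) = 33%.
- Smallest: 1,703·15,605/2,903,887/4 = 2.3 arrests; ×0.05 = 0.11 survivors; no survivor in 89% of quarters.
- Largest: 1,703·774,072/2,903,887/4 = 113 arrests; ×0.05 = 5.7 survivors.

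**Power for a 2-point level change with a linear trend and a known change point.** Weighted least squares on quarterly proportions with intercept, trend and change term. Power = Φ(2/SE − 1.96), with SE in points. Only significance in the right direction counts, so values below 5% can occur. Assumptions: 12 run-in quarters (2004–2006); 7 after-quarters, from 2,962/1,703 = 1.74 years, and also 12; 7 to 40 before-quarters, 40 being 1994–2003; no autocorrelation. The change is a step in early 2005, a ramp over 2004–2005, or a step with the run-in left out.

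| Unit | Before/after quarters | Step: SE, power | Ramp: SE, power | Run-in omitted: SE, power |
|---|---|---|---|---|
| Average community | 7/7 | 3.91, 7% | 6.36, 5% | 12.85, 4% |
| Average community | 40/12 | 2.19, 15% | 2.50, 12% | 2.93, 10% |
| All 19 pooled | 7/7 | 0.90, 61% | 1.46, 28% | 2.95, 10% |
| All 19 pooled | 40/7 | 0.51, 98% | 0.59, 93% | 0.71, 80% |

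Over the same scenarios the largest community has 5–54% power and the smallest 3–5%.

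**Homogeneity.** An average community's SE is 2.2 to 12.9 points, against an effect of 2. Even with no trend term, 2,962/19 = 156 patients per phase gives a 95% half-width of 1.96·√[(0.0475 + 0.0651)/156] = 5.3 points. Communities with no effect and communities with twice the target could not be told apart.

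**Change point.** The article states no search rule. If the change point were searched over the 12 run-in quarters and judged at 1.96, simulation under no change gives a false-positive rate of about 23–33%, against 5% for a fixed point. The range covers pooled and average-community series with 7 or 40 before-quarters.

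**Bystander CPR.** At a baseline of 15–16.7%, an average community has 22.4·0.15 = 3.4 to 22.4·0.167 = 3.7 events per quarter, about three times the survivor count.

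**The case against.** A reader might infer that the study cannot answer its survival question. The document does not support that. The same sentence that sets the community-level analysis also provides for a meta-analysis, and pooled power runs from 10% to 98% depending on a before-series length the article does not state. Inadequacy is shown for single communities only. Even there the estimates are imprecise rather than impossible: an average community has about 1.12·26 = 29 survivors over 26 quarters.

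It is also tempting to call the before-after model uncontrolled. It is not. It adjusts for four named factors, and the list is worded as open. The accurate statement is that no calendar-time or community term is listed.

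The size of any secular change is unknown. If the before sample is as long as the after sample and ends at 2004, the phase midpoints are 3 + 1.74 = 4.74 years apart, so each 0.1 point of yearly drift would add about 0.47 points. The document gives no evidence of drift, so this is an illustration and not a measure of bias. The Background does say that "PAD programs received the highest endorsement from the American Heart Association" following a trial published in 2004. It does not date the endorsement itself, and it argues that gains in public places would have limited effect on overall survival because 85% of arrests are residential.

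Two further points stand in part. Identifying an inflection need not mean an uncorrected search, and a condensed article may leave the rule to a fuller plan, so the inflated error rate is conditional. Trend adjustment also costs power, and a sharp step may fit a gradual introduction badly. Both belong in the remedy. They do not rescue an optional pooling step.

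**Conclusion.** The concern holds for survival. The only analysis stated to control for trend is fixed at a level with about 1.1 survivors per quarter on average (about 0.1 to 5.7 by population) and roughly 4–15% power for the 2-point target in an average community. Whether it can say anything useful depends on pooling, which the plan leaves optional after a check with almost no information. Leaving the change point open adds an avoidable risk of false positives, of about 23–33% only if it is searched within the run-in without correction.

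The event counts follow from the article's figures, with the community range assuming arrests proportional to population. The power figures assume independent quarters, a linear trend, two-sided 0.05 and the phase lengths shown. The conclusion for an average community holds across all the lengths tried. The pooled conclusion does not, which is why the before-series length has to be stated. For bystander CPR the point is weaker.

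**What to change.** For survival, replace the per-community series and optional meta-analysis with one committed patient-level segmented logistic model across all 19 communities. It should include:

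- community effects and between-community variation in the programme effect;
- calendar time, with the run-in quarters kept in;
- the change set in advance from each community's start date, with a pre-stated step or phase-in form.

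Keep the community series as descriptive displays. Report the pooled model alongside the before-after logistic comparison, and rest any claim that the programme rather than secular change altered survival on the trend-adjusted estimate. State the length of the before series and the power of this model, and make clear that the 90% applies to the two-sample comparison without trend.

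The cost is analysis wording, 19 start dates and somewhat more modelling. The downside is lower power than the simple comparison if the before series is short: about 10–61% with seven before- and seven after-quarters, against 80–98% with data from 1994. Since the centres report collecting data since 1994, a long before series appears to be available.

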### Sample size

The main objective of this study is to measure the effect of dispatch-assisted CPR instructions on survival to hospital discharge for out-of-hospital cardiac arrest victims. The required sample size has been estimated based on a dichotomous response variable from two independent samples (before and after the introduction of dispatch-assisted CPR instructions). The required sample size is based on an expected survival rate of 5% in the before group (based on previous studies conducted in the study communities [8]), an expected survival rate of 7% in the after group (based on mathematical modelling and scientific reports), an average survival rate of 6% for all study participants and a 2% minimal clinically important difference in survival rate. Using these figures and setting power at 90%, 2,962 cardiac arrest victims will be required for each group.

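### The 90% power and the patient-level before-after test allow for no variation between the 19 communities in the before-after change; the cost is small or material depending on a spread the protocol does not give

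*Protocol article*

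**What the plan says.** The Sample size section names survival to discharge as the main objective. The required number is "estimated based on a dichotomous response variable from two independent samples (before and after the introduction of dispatch-assisted CPR instructions". The inputs are "an expected survival rate of 5% in the before group", "an expected survival rate of 7% in the after group" and "an average survival rate of 6% for all study participants and a 2% minimal clinically important difference in survival rate"; the result is "setting power at 90%, 2,962 cardiac arrest victims will be required for each group". No allowance for community is mentioned.

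Under Bystander CPR and Survival Rates, two approaches are to be considered, and neither is named primary. The first is "A univariate and a stepwise logistic regression analysis to control for potential confounding effects of variables possibly associated with bystander CPR and survival rates", comparing before with after. The variables it names are age, gender, initial rhythm and response times. The second is a quarterly time series run separately in each community, after which "the results may be combined in a meta-analysis after assessing homogeneity of the results across the communities".

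Study design and setting (text after Figure 1) describes the units: "The combined population in those 19 communities is 2,903,887 and ranges between 15,605 and 774,072". All centres began the instructions between 2004 and 2005. The before phase is prior to 2004 and the after phase starts in 2007, so every community contributes to both.

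**The concern.** Whether a patient falls in the before or the after group is settled by community and era, not patient by patient. A patient-level comparison counts only patient-to-patient variation as error. If survival moves by different amounts in different communities between the two eras, for reasons unrelated to the instructions, that local movement is also error in the pooled phase effect. With 19 communities, one of them holding more than a quarter of the population, it averages out slowly.

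At stake are the 95% interval and test for the main objective, the same analysis for bystander CPR, and the 90% power statement. This is separate from a province-wide trend, because it arises even when the average background change is zero.

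**Working it through.** **Inputs.** From Sample size: 5% v 7%, mean 6%, 90% power, n = 2,962 per group. From Study design and setting: 19 communities, total 2,903,887, smallest 15,605, largest 774,072. Assumed: two-sided 5% (alpha is not stated); patients in proportion to population; τ, the SD across communities of the true before-after change, from 0 to 1.5 percentage points.

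**1. Reproduce the plan's figure.**

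n = [1.960 √(2 × 0.06 × 0.94) + 1.282 √(0.05 × 0.95 + 0.07 × 0.93)]² / 0.02² = [1.960 √0.1128 + 1.282 √0.1126]² / 0.0004 = 2,961.02, rounded up to 2,962.

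One-sided testing gives 2,414 and a continuity correction gives 3,061. The stated figure is therefore correct for independent patients and contains nothing for community.

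**2. What cancels.** Let community c have share w_c in both phases, level u_c and change d_c. The pooled change is Σw_c(u_c + d_c) − Σw_c u_c = Σw_c d_c. The levels drop out; the changes stay. So

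Var = 0.1128/n + τ²H, with H = Σw_c².

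The first term is 0.1128/2,962 = 3.81 × 10⁻⁵, which gives a naive SE of 0.617 points.

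**3. Bound H.** The largest share is 774,072 / 2,903,887 = 26.7%. The 17 communities of unstated size total 2,903,887 − 774,072 − 15,605 = 2,114,210.

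- All 19 equal (contradicts the stated range, so only a best case): H = 1/19 = 0.053.
- The 17 equal: H = 0.102, or 1/H = 9.8 effective equal communities.
- Smooth decline from largest to smallest: H = 0.134, or 7.5.
- As unequal as the figures allow (three at 774,072, one at 347,596, fifteen at 15,605): H = 0.228, or 4.4.

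**4. Consequences at 2,962 per group.** Type I error of the patient-level test = 2[1 − Φ(1.96 × SE_naive / SE_true)]. Power with the correct SE = Φ[(0.02 − 1.96 SE_true) / √(0.1126/n + τ²H)].

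Example, τ = 1 point and H = 0.228: Var = 3.81 × 10⁻⁵ + 2.28 × 10⁻⁵ = 6.09 × 10⁻⁵, so SE = 0.780 points, 1.264 times the naive SE. Type I error = 2[1 − Φ(1.551)] = 12.1%. Power = Φ(0.604) = 73%.

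| τ (points) | All equal (19) | 9.8 effective | 7.5 effective | 4.4 effective |
|---|---|---|---|---|
| 0 | 5.0% / 90% | 5.0% / 90% | 5.0% / 90% | 5.0% / 90% |
| 0.5 | 5.4% / 89% | 5.8% / 88% | 6.0% / 87% | 6.8% / 86% |
| 1.0 | 6.6% / 86% | 8.2% / 82% | 9.2% / 80% | 12.1% / 73% |
| 1.5 | 8.7% / 81% | 12.2% / 73% | 14.3% / 68% | 20.1% / 56% |

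(Type I error / power, normal approximation.)

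**5. Simulation check.** With smooth-decline sizes and 20,000 studies per setting, the pooled z-test rejected 4.9%, 9.7% and 16.2% of the time at τ = 0, 1.0 and 1.5 with no mean effect. The last two are slightly above the table because the simulation holds survival at 5%, where sampling variance is smaller than at 6%.

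**6. Does a community main effect help?** A separate simulation used unequal sizes (6.9 effective communities), an ICC of 0.01 and a correlation of 0.8 between a community's before and after rates. That implies τ = √(2 × 0.01 × 0.05 × 0.95 × 0.2) = 1.4 points. False-positive rates were 14.9% for crude logistic regression, 15.2% stratified by community, and 4.6% for a community-level clustered test with a t reference. Stratifying removes what already cancels and leaves the rest.

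**The case against.** The strongest reply is that everything turns on τ, which the documents do not supply. At 0.5 points the loss is slight, and at zero the plan is exactly right. This stands: the direction is certain for any τ above zero, but the size is conditional.

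Second, community is already in the plan. The time series runs by community and checks homogeneity, so it would be wrong to say the plan ignores the issue. But that approach is only to be considered, its pooling is optional, and the sample size does not rest on it.

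Third, the article condenses a fuller plan, the list of variables is not closed, and the method for standard errors is not stated. A statistical analysis plan could add clustering to the regression. That is fair for the regression, which can be judged only as described. It does not reach the power statement, where independence is explicit.

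Fourth, 2,962 is a requirement rather than a cap, and about 1,703 arrests are treated each year. More patients would raise power, but they shrink only the first variance term. The ratio of true to naive variance, 1 + τ²Hn/0.1128, grows with n, so the patient-level test's type I error gets worse.

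A reader might go further and assume an ICC of 0.05, where the simulations give 23-38% false positives and 27-46% power (correlation 0.8). The documents do not support that setting. It implies a between-community SD of √(0.05 × 0.05 × 0.95) = 4.9 points around a 5% mean, and a change SD of √(2 × 0.05 × 0.05 × 0.95 × 0.2) = 3.1 points, larger than the 2-point target. The Background says survival rarely exceeds 5%.

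**Conclusion.** The point holds in conditional form. The stated power and the before-after regression as described leave out one variance component: variation between communities in the before-after change. The homogeneity check shows that the authors regard such variation as possible. Its effect is small at an SD of 0.5 points and material from about 1 point upward, as tabulated. The favourable end of each range takes all 19 communities as equal, which the stated populations rule out.

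The results rest on an inferred two-sided 5% level, case shares proportional to population, and communities changing independently. If several share a dispatch centre there are fewer independent units and the effect is larger. Using t in place of normal critical values would lower the power figures somewhat.

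Bystander CPR is affected in the same way: 9-15% false positives in simulation at ICC 0.01 and correlation 0.8. Power for a change as large as the pilot's (16.7% to 26.4%) stayed at 95% or more.

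It should not be inferred that 2,962 is miscalculated, that stable differences between communities bias the comparison, or that the intervals are known to be badly wrong.

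**What to change.** In the first modelling approach, base the phase-effect test and 95% interval for survival and for bystander CPR on standard errors clustered on community, with a small-sample correction and t reference, or on a community-level paired analysis. A community main effect alone is not enough. A logistic model with a random community-by-phase effect can serve as a sensitivity analysis. It should not lead: it was not among the methods simulated, and the smallest community expects about 2,962 × 15,605 / 2,903,887 = 16 patients and 0.8 survivors per phase. Report the between-community spread of the phase effect.

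In Sample size, state that 90% power assumes independent patients and the same change in every community. Restate power over a plausible range of community-by-phase variation, estimated from the data these centres have collected since 1994.

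The cost is analysis wording and a restated power figure. Community is known for every patient and no extra patients are needed. The downside is wider intervals and a less favourable stated power.

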### Ethics approval

Research ethics board approval was obtained from The Ottawa Hospital (protocol #2007233-01H). As the study will not affect usual practice, there were no specific ethical concerns. Informed consent is not required because it is impossible to obtain in emergency situations such as cardiac arrest, and because patients will not be randomized to receive different therapies. No identifying information on either the dispatcher or the patient will be recorded.

